## Background

Laparoscopic surgery for colorectal cancer is becoming more common worldwide and has demonstrated superiority to open surgery regarding short-term outcomes [1–3] and non-inferiority regarding long-term outcomes [4–6]. Among laparoscopic colorectal resections, right-sided colectomy is a relatively safe procedure, with few complications. An annual report of a Japanese nationwide survey in 2020 indicated that right hemicolectomy had a lower complication rate (8.0%) compared to low anterior rectal resection (11.1%) [7]. However, right hemicolectomy had a high 30-day mortality rate of 1.4%, four times more than that of low anterior rectal resection, which is a more difficult procedure with a higher complication rate [7]. More than 30% of patients undergoing right hemicolectomy are older than 80 years, which is more than twice as many as those undergoing low anterior rectal resection [8]. This older population might include many high-risk patients, and surgery might be indicated regardless. One hypothesis is that postoperative mortality following right hemicolectomy is primarily influenced by non-operative factors such as advanced age and frailty. However, operative factors — including intraoperative complications and delayed recognition of clinical deterioration — may also play a role. In other words, a single complication may present more severely, with a delayed response exacerbating severity. Therefore, further scientific investigation is required to clarify the factors affecting severe complications, including mortality, after laparoscopic right-sided colectomy.

Regarding procedural issues, intraoperative vascular injury remains a major complication of this technique. Injury to the superior mesenteric vein (SMV) and surrounding vasculature can cause major bleeding and subsequent massive bowel resection. Approximately 3% of D3 dissections result in vascular injury [8]. Moreover, minor injuries that do not result in major bleeding may be encountered clinically; however, they do not significantly affect final outcomes. Nevertheless, clinicians, particularly young surgeons, should be aware of these risks to safely perform the procedure. Clarifying the frequency and risk factors of intraoperative vascular injuries is crucial. Therefore, we designed the current prospective observational study to investigate factors affecting the intraoperative vascular injury rate as additional safety indicators.

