### Endpoints

The primary endpoint is the incidence of postoperative complications (Clavien–Dindo classification grade ≥ III) [35]. The rate of severe postoperative complications in all eligible patients will be investigated, and risk factors affecting them will be determined.

A key secondary endpoint is the incidence of intraoperative vascular injury around the SMV. The rate of intraoperative vascular injury around the surgical trunk in all eligible patients will be investigated, and risk factors affecting it will be extracted.

Other secondary endpoints include the incidence of postoperative complications (Clavien–Dindo classification grade ≥ II), 5-year overall survival, recurrence-free survival, and other short- and long-term outcomes (operative time, blood loss, conversion rate, degree of lymph node dissection, intraoperative complication rate, reoperation rate, R0 resection rate, local recurrence rate in the whole cohort and by stage, and incidence of bowel obstruction and herniated abdominal wall scarring). Factors influencing the above endpoints will be determined for all eligible patients. Furthermore, comparisons will be made between each subgroup, as shown in Table 1.

**Table 1 Tab1:** Secondary endpoints

1. Short-term results by approach (a. Medial approach vs. retroperitoneal approach; b. Medial approach vs. cranial approach; c. Retroperitoneal approach vs. cranial approach; a–c for laparoscopic surgery and robotic surgery, respectively)
2. Short-term results of robot-assisted and laparoscopic surgery (Comparison in all approaches, medial approach, retroperitoneal approach, and in each ASA-PS, respectively)
3. Short-term results by degree of lymph node dissection (D2, D3v, D3a)
4. Long-term results by approach, robot or laparoscopy, and degree of dissection
5. Impact of experience on short-term and long-term outcomes after the surgery performed by the surgeons before obtaining board certification in gastrointestinal surgery (including the investigation by each approach, robot/laparoscopy, and degree of lymph node dissection)
6. Impact of surgeons’ case volume prior to obtaining board certification in gastrointestinal surgery on short- and long-term outcomes following robot-assisted procedures
7. Impact of the participation of Endoscopic Surgical Skill Qualification-certified surgeons in surgery and their role in the procedure on short- and long-term outcomes
8. Impact of anastomosis method on short- and long-term outcomes

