(23) Final bleeding control: possible/impossible (operative death).(24) Timing of intraoperative vascular injury: during lymph node dissection, mobilisation, intracorporeal anastomosis, extracorporeal anastomosis, and others (described at the time of adhesion dissection, drain insertion, etc.).(25) Other intraoperative complications: list those requiring intraoperative intervention (e.g., injury to other organs).(26) Open conversion: a skin incision ≥ 8 cm is generally defined as an open conversion. However, if the incision exceeds 8 cm solely for the purpose of tumor extraction, it shall not be considered an open conversion.(27) Postoperative complications (within 30 days): Clavien–Dindo classification grade ≥ II should be used.(28) Date of onset of anastomotic leakage/deep SSI: the date of onset is defined as the earliest time of abnormality during the initial physical examination, such as fever, abdominal pain, abnormal discharge from the drainage tube, blood test, and imaging.(29) Treatment intervention date: the date of treatment intervention is defined as the date corresponding to any of the following: administration of medical therapy (in the case of Clavien–Dindo classification grade II); performance of endoscopic, surgical, or interventional radiology (IVR) procedures without general anesthesia (grade IIIa); performance of endoscopic, surgical, or IVR procedures with general anesthesia (grade IIIb); or admission to the intensive care unit (ICU) (grade IV). Additionally, in cases of anastomotic leakage or deep surgical site infection (SSI), the date should be recorded if a new percutaneous drain is inserted or an existing one is replaced.(30) 30-day death: death from any cause within 30 days of surgery.(31) Surgical death: 30-day death or death during hospitalisation 31–90 days postoperatively.(32) Histological type, pathological stage, T and N stages, and R status: according to the Japanese Classification of Colorectal, Appendiceal, and Anal Carcinoma, third English Edition [37].(33) Postoperative adjuvant therapy: indicate whether at least one course has been completed, and specify the type of chemotherapy administered.(34) Recurrence-free survival: duration from the date of first treatment (surgery or start of preoperative therapy) to the date of the last confirmed recurrence-free/recurrence.(35) Local recurrence: local recurrence will be assessed based solely on the initial recurrence, with distinctions made between lymph node recurrence, anastomotic site recurrence, and other locations.(36) Intestinal obstruction during follow-up (Clavien–Dindo classification grade ≥ II): only the first occurrence 30 days after surgery will be considered.(37) Abdominal wall scar hernia: this will be diagnosed based on imaging findings, such as CT, or palpation of the hernia in the surgical scar. Only the first occurrence 30 days after surgery will be considered.

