Secondary endpoints: Summary statistics for patient background and other surgical outcomes will be calculated. A multivariate logistic regression or multiple regression analysis will be performed using the factors listed in the survey items that may influence outcomes. A random-effects model will be used to account for differences between the centres. The main endpoint for short-term outcomes for each subgroup is postoperative complications (Clavien–Dindo classification grade ≥ II), and group comparisons will be conducted after propensity score matching (differences between groups will be tested using Student’s t-test and the χ^2^ test) and logistic regression to identify confounders. Multiple regression analysis will be used to analyse continuous variables. A random-effects model will be used to account for the differences between institutions. The Kaplan–Meier method will be used to plot cumulative late complication curves, local and overall recurrence-free survival curves, and overall survival curves for long-term outcomes. To account for confounding factors, a multivariate Cox regression analysis will be performed using preoperative and postoperative factors that may contribute to recurrence and late complications, and risk factors will be examined. In addition to regression analysis of factors, each factor will be discussed from clinical and medical perspectives to reach a combined perspective.

The number of experienced cases will be added to the factors in the multivariate analysis to examine their effect on the outcome. The correlation of the number of cases experienced and outcomes (operation time and blood loss) with the learning curve will be evaluated using the moving average method and the cumulative sum curve.

Statistical significance will be set at *p* < 0.05.

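### Recurrence-free survival is defined without death as an event, so it measures time to recurrence and will look too favourable

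*Protocol article*

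**What the plan says.** Endpoints lists, among the other secondary endpoints, "5-year overall survival, recurrence-free survival, and other short- and long-term outcomes". RFS and overall survival are thus separate outcomes.

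Definition of assessment data, item 34, gives the definition: "Recurrence-free survival: duration from the date of first treatment (surgery or start of preoperative therapy) to the date of the last confirmed recurrence-free/recurrence". The same list defines death explicitly where it is wanted (item 30, 30-day death; item 31, surgical death), but item 34 does not mention it. On local recurrence, item 35 says that "local recurrence will be assessed based solely on the initial recurrence". Items 36 and 37 restrict obstruction and scar hernia to the first occurrence. None of these three mentions death.

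Statistical analysis says: "The Kaplan–Meier method will be used to plot cumulative late complication curves, local and overall recurrence-free survival curves", together with overall survival curves. For factors, "a multivariate Cox regression analysis will be performed using preoperative and postoperative factors that may contribute to recurrence and late complications". No competing-risk method is named, and no rule is given for patients who die.

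Observation, investigation data, and methods lists survival outcome, the date it was last confirmed, the date recurrence was confirmed and the type of first recurrence. Its only censoring rule concerns pathological stage 0 and IV.

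**The concern.** RFS is ordinarily read as the probability of being alive and free of recurrence. Item 34 offers two ways for the clock to stop: recurrence (an event) or the last date known to be recurrence-free (censoring). A death without recurrence can only fall under the second. This holds even if the date of death is taken as the last recurrence-free date.

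The difference matters when deaths from other causes are common. The article gives reason to expect that. Background reports that "More than 30% of patients undergoing right hemicolectomy are older than 80 years", cites a 30-day mortality of 1.4%, and puts forward age and frailty as possible drivers of death. Under item 34 even a postoperative death would not count against RFS. The reported figure would be too high, would not be comparable with studies that count death, and would carry into the long-term comparisons by approach, platform and dissection level (Table 1, item 4).

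**Working it through.** **Is there a figure to reproduce?** No. The article states no RFS, 5-year recurrence or 5-year mortality figure. Direction follows from the definition; size needs assumptions.

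**Inputs for RFS (assumed).** 5-year cumulative hazard of recurrence H_r = 0.17. 5-year cumulative hazard of death without recurrence H_d = 0.13, range 0.08 to 0.25. Hazards constant over time.

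**Formulas.** RFS as item 34 defines it (death censored) = exp(−H_r). RFS with death as an event = exp(−(H_r + H_d)).

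| H_d | RFS as defined | RFS with death counted | Overstatement |
|---|---|---|---|
| 0.08 | exp(−0.17) = 84.4% | exp(−0.25) = 77.9% | 6.5 points |
| 0.13 | 84.4% | exp(−0.30) = 74.1% | 10.3 points |
| 0.25 | 84.4% | exp(−0.42) = 65.7% | 18.7 points |

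**Wider assumptions.** Take a net 5-year recurrence risk of 5% to 20% and a net risk of death without recurrence of 5% to 30%. The gap then runs from 4.0 points (80.0% against 76.0%) to 28.5 points (95.0% against 66.5%). The direction never changes.

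**A lower anchor from the article.** If the 1.4% 30-day mortality in Background were the only death without recurrence, then at 80% RFS the gap would be 0.80 × 0.014 = 0.011, about 1.1 points.

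**Late complications and local recurrence.** Here the quantity of interest is cumulative incidence. Assume a 5-year cumulative hazard H_c = 0.12 for the complication and H_d = 0.20 to 0.40 for death.

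- One minus Kaplan–Meier with death censored: 1 − exp(−0.12) = 11.3%.
- Cumulative incidence (Aalen–Johansen): H_c/(H_c + H_d) × [1 − exp(−(H_c + H_d))].
  - H_d = 0.20: 0.12/0.32 × (1 − exp(−0.32)) = 0.375 × 0.274 = 10.3%.
  - H_d = 0.40: 0.12/0.52 × (1 − exp(−0.52)) = 0.231 × 0.405 = 9.4%.

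The overstatement of incidence is 1.0 to 1.9 points. Over the wider grid, one minus Kaplan–Meier exceeds cumulative incidence by a factor of about 1.03 to 1.19 (0.1 to 3.1 points). This error makes results look worse, the opposite direction from RFS.

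**The case against.** The strongest defence is that this is a condensed article. Censoring and competing-risk detail commonly sits in a full protocol or SAP, and neither is shown. That stands for the late-complication and local-recurrence curves: the article names Kaplan–Meier and is silent on death, so censoring at death is an inference there. It does not stand for RFS. Item 34 is a printed definition, complete in form, and a SAP that counted death would contradict it.

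It can also be said that deaths are not lost, because 5-year overall survival is a separate endpoint with its own curves. That is right. A reader might infer that the long-term comparisons ignore deaths altogether, and the article does not support this. But a separate overall survival curve does not correct a mislabelled RFS curve.

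The sizes rest on assumed hazards, and the age figure comes from a background survey, not from this cohort of clinical stage 0 to III patients having laparoscopic or robotic surgery. Both objections stand. They limit what can be said about magnitude, not direction.

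Further readings are tempting but not supported:

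- **All long-term results look better than they are.** This is true of the recurrence-free survival curves, but the incidence of late complications and local recurrence would look worse.
- **Adjuvant therapy brings immortal-time bias.** Item 33 asks sites to "indicate whether at least one course has been completed", and the Cox models admit postoperative factors. But adjuvant therapy is not named as a covariate, and no adjuvant effect is among the Table 1 comparisons.
- **The clock start is wrong.** Starting at preoperative therapy is a stated and consistent origin, and no effect on the results can be shown from the article.
- **The Cox models need replacing.** A Cox model for recurrence with deaths censored already estimates the cause-specific hazard.

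**Conclusion.** The RFS definition is a real defect. As written, death without recurrence is not an event, the endpoint is time to recurrence, and the RFS curves will be too favourable. Under assumed cumulative hazards of 0.17 for recurrence and 0.08 to 0.25 for death without recurrence, the overstatement at 5 years is about 6 to 19 points. The article supplies no rates that would narrow this range.

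The competing-risk point is secondary and conditional. If deaths are censored in the late-complication and local-recurrence analyses, their incidence is modestly overstated, for example 11.3% against 9.4% to 10.3% under assumed hazards.

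Severity is moderate. RFS is one of several other secondary endpoints; the primary endpoint (grade III or higher complications), the key secondary endpoint (vascular injury) and overall survival are untouched. The long-term analysis waits for 5 years of follow-up in all patients, so there is time to correct the wording before any such result exists.

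**What to change.** Reword item 34 so that RFS runs from the stated origin to first recurrence or death from any cause, whichever comes first, with patients alive and recurrence-free censored at the last date confirmed as such. If time to recurrence is what the investigators want, keep the present end dates and rename the endpoint and its curves accordingly.

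In Statistical analysis, state that the cumulative curves for obstruction and scar hernia, and the incidence of local recurrence, will use the Aalen–Johansen estimator with death as a competing event. The Cox models for recurrence can stay as planned.

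The cost is wording only. Survival outcome, recurrence status and their dates are already on the data list, so no new collection is needed. The price is a less favourable RFS figure; the late-complication and local-recurrence incidences would come out slightly lower than from one minus Kaplan–Meier with deaths censored.

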
### Target number of cases

The target number of cases for the study is 2,000; nevertheless, we aim to recruit as many cases as possible within the study period.

The rationale for setting the target number of cases is described below.

The postoperative complication rate (grade ≥ III) of laparoscopic surgery in all patients with colon cancer in a Japanese randomised controlled trial (RCT) (JCOG0404) was 4.6% [3]. The postoperative complication rate (grade ≥ III) for laparoscopic CME of right colon cancer in a Norwegian RCT was 6.1% [10]. Based on these reports, we calculated that a sample size of approximately 2,000 cases is required to achieve a postoperative complication rate (grade ≥ III) of 5% and a 95% confidence interval within ± 1.0% based on the binomial distribution in this study.

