**Methods:**

Patients undergoing laparoscopic or robot-assisted surgery for right-sided colon cancer at participating institutions in the Laparoscopic Colorectal Resection Study Group will be prospectively enrolled between 3 July 2024 and 31 May 2026. This multicenter study expects to enroll a total of 2,000 colorectal cancer cases from 73 facilities nationwide. The primary endpoint is the incidence of postoperative complications classified as Clavien–Dindo grade ≥ III. Risk factors contributing to these severe complications will be analysed. As a key secondary endpoint, the incidence and predictors of intraoperative vascular injury near the superior mesenteric vein will also be evaluated.

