### Statistical analysis

The analysis of primary endpoints, key secondary endpoints, and other secondary endpoints regarding short-term outcomes will begin as soon as 120 days after the patient enrolment period ends. Long-term outcome analysis of the secondary endpoint shall be performed upon completion of the 5-year follow-up period for all enrolled subjects.

Primary/key secondary endpoints: Summary statistics of patient background and surgical outcomes will be calculated, and the proportion of major complications and intraoperative vascular injury around the SMV and their causes will be summarised. Logistic regression analysis will be performed using the factors listed in the survey items that may influence the rate of major complications and intraoperative vascular injury around the SMV. A random-effects model will be used to account for the differences between institutions. Patients who underwent open conversion before the lymph node dissection will be excluded from the analysis of key secondary endpoints, and the relationship between the extent and location of the damaged vessel and the magnitude of the effect on the perioperative period will be considered.

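### The ±1.0-point precision that justifies 2,000 cases assumes independent patients, although the plan spreads them over 73 institutions that it expects to differ

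*Protocol article*

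**What the plan says.** The section on the target number of cases in the protocol article cites two earlier grade ≥ III rates. One comes from a Japanese randomised trial in colon cancer generally ("JCOG0404) was 4.6" per cent). The other is specific to the right colon ("laparoscopic CME of right colon cancer in a Norwegian RCT was 6.1" per cent). The section then states that about 2,000 cases "is required to achieve a postoperative complication rate (grade ≥ III) of 5" per cent with "a 95% confidence interval within" ± "1.0% based on the binomial distribution in this study". The type of interval is not named, and neither an ICC nor a design effect appears. The figure is a target and not a ceiling: "The target number of cases for the study is 2,000; nevertheless, we aim to recruit as many cases as possible within the study period".

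The abstract's methods expect "2,000 colorectal cancer cases from 73 facilities nationwide". For the primary and key secondary endpoints, the statistical analysis section says that the proportions will be summarised and that logistic regression will look for risk factors. It adds: "A random-effects model will be used to account for the differences between institutions".

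**The concern.** The sizing and the analysis rest on different views of the same data. A binomial calculation treats all 2,000 patients as independent with one common risk. The analysis section allows for risk that varies between institutions. If it does vary, patients within an institution are positively correlated, and the variance of the overall proportion exceeds the binomial variance.

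Variation between institutions is plausible on the document's own account. The survey figures describe the preferred approach and anastomosis institution by institution, institution type and size are collected, and all of these are candidate influences on safety.

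The overall incidence is the primary endpoint. If its interval is later reported as a simple binomial one, it will be too narrow and will cover the true rate less often than 95%.

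**Working it through.** **Inputs from the protocol article:** n = 2,000; assumed rate p = 5%; two-sided 95% interval; target half-width 1.0 point; cited rates 4.6% and 6.1%; 73 institutions, so mean size m = 2,000/73 = 27.4.

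**Assumptions, not in the documents:** ICC of 0.003, 0.01 or 0.02; coefficient of variation (CV) of institution size of 0 (equal sizes) or 0.8.

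**Step 1. Reproduce the plan's figure.** Half-width = 1.96 × √(p(1−p)/n) = 1.96 × √(0.05 × 0.95/2,000) = 0.955 points. The smallest n for 1.0 point is 1.96² × 0.0475/0.01² = 1,825. About 2,000 therefore meets the target with some 175 cases to spare. At n = 2,000 the half-width stays within 1.0 point up to a rate of about 5.5%.

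**Step 2. How much clustering the margin can absorb.** The design effect is DE = 1 + ((1 + CV²)m − 1) × ICC, and the half-width grows by √DE. The largest DE that still gives 1.0 point is (1.0/0.955)² ≈ 1.096.

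- Equal sizes: break-even ICC = 0.096/(27.4 − 1) ≈ 0.0036.
- CV 0.8: (1 + 0.64) × 27.4 − 1 = 43.9, so break-even ICC = 0.096/43.9 ≈ 0.0022.

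As a standard deviation of true institutional rates around 5%, √(ICC × 0.0475), these are about 1.3 and 1.0 points.

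**Step 3. Half-width in points under assumed ICCs.** Each cell gives equal sizes, then CV 0.8.

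| ICC | DE | Rate 4.6% | Rate 5% | Rate 6.1% |
|---|---|---|---|---|
| 0 | 1 | 0.92 | 0.96 | 1.05 |
| 0.003 | 1.08 / 1.13 | 0.95 / 0.98 | 0.99 / 1.02 | 1.09 / 1.12 |
| 0.01 | 1.26 / 1.44 | 1.03 / 1.10 | 1.07 / 1.15 | 1.18 / 1.26 |
| 0.02 | 1.53 / 1.88 | 1.13 / 1.26 | 1.18 / 1.31 | 1.30 / 1.44 |

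The effective sample size, 2,000/DE, is 1,582 / 1,390 at ICC 0.01 and 1,309 / 1,065 at ICC 0.02.

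**Step 4. Coverage if a simple binomial interval were used.** Coverage ≈ 2Φ(1.96/√DE) − 1. At ICC 0.01 this is 92% (equal sizes) or 90% (CV 0.8). At ICC 0.02 it is 89% or 85%.

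**The case against.** The strongest reply is that the stated figure is right on its stated terms and that no failure has been shown. Without an ICC in the documents, any shortfall is conditional, and a range starting at 0.01 would begin above break-even. That is fair, and is why 0.003 is in the table: with equal sizes the target is still met there. The Discussion also asserts that institutional experience will not affect outcomes at these proficient centres. It offers no data for this, however, and the analysis section still provides for institutional differences.

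It can also be said that the random-effects sentence follows the regression and may not concern the headline proportion, and that the interval for that proportion is not named and could sit in an analysis plan that is not shown. Both hold. The coverage figures therefore apply only if a simple binomial interval is used. The sizing statement itself is in the article and rests on independence.

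Two stronger readings are tempting, and the documents support neither:

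- A reader might infer that the figure is an arithmetic error, or that it fails with an exact interval. The exact interval for 100/2,000 is 4.09–6.05%, a half-width of 0.98. Only its upper arm passes 1.0, by 0.05 point, and the plan names no interval type and says approximately.
- A reader might infer that the plan breaks its promise because the half-width is 1.05 at the cited 6.1%. The plan states its precision at 5% only, and at the other cited rate, 4.6%, the half-width is 0.92. This is sensitivity to the assumed rate.

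Finally, 2,000 may be exceeded, which would recover some precision, although the Discussion calls case accumulation a major operational challenge.

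**Conclusion.** The concern holds in a limited form. The ±1.0 points is correct for independent cases at a rate of about 5%, but it makes no allowance for the institutional differences that the same document plans to model, and the spare margin is thin. At 5%, assumed ICCs of 0.01–0.02 put the half-width 0.07 to 0.31 points above target, depending on how unequal the institutions are. An ICC of 0.003 with equal sizes leaves it just within target.

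The conclusion rests on the assumed ICCs and size variation and on the usual design-effect formula. The practical loss is modest: no test, threshold or stopping decision hangs on this proportion, and the target of 2,000 remains reasonable. This is an inexpensive improvement in how precision is stated and computed.

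**What to change.** Keep the target of 2,000 and make two changes of about a sentence each.

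1. In the section on the target number of cases, say that ±1.0 points assumes a 5% rate and independent cases. Give the expected half-width over 4.6–6.1% and a range of ICCs labelled as assumed, from about ±0.9 (4.6%, no clustering) to about ±1.4 (6.1%, ICC 0.02, size CV 0.8).
2. In the statistical analysis section, state that the 95% interval for the primary proportion will allow for institution, either with a cluster-robust variance or as the marginal proportion from the random-effects model, in place of a simple binomial interval.

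The cost is a slightly less favourable stated precision and probably a somewhat wider reported interval. No additional patients or data are needed.
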